# Remotely controlled mandibular positioning of oral appliance therapy during polysomnography and drug-induced sleep endoscopy compared with conventional subjective titration in patients with obstructive sleep apnea: protocol for a randomized crossover trial

**DOI:** 10.1186/s13063-019-3698-4

**Published:** 2019-10-29

**Keywords:** Mandibular advancement device, Sleep-disordered breathing, Apnea–hypopnea index

## Abstract

**Background:**

The amount of mandibular protrusion is a key factor in optimizing the efficacy of mandibular advancement device (MAD) therapy in an individual patient diagnosed with obstructive sleep apnea. This process is called titration and is generally based on resolution of subjective symptoms like snoring and/or daytime sleepiness as a function of protrusion. An objective approach uses a remotely controlled mandibular positioner (RCMP) during a full-night polysomnography (PSG), in analogy with continuous positive airway pressure (CPAP) titration. More recently, the feasibility of RCMP use during drug-induced sleep endoscopy (DISE) titration was reported.

**Methods:**

This randomized crossover trial will compare DISE-assisted titration to PSG-guided titration, as well as with the conventional subjective titration method. The primary outcome is the actual mandibular protrusive position found to be the most optimal for each tested titration procedure. Furthermore, the therapeutic efficacy will be compared among the different titration modalities using level 1 sleep studies.

**Discussion:**

Currently, the optimal titration of MAD therapy is most often based on ‘trial and error’. The conventional method relies on subjective improvement in symptoms, although this may not provide the most accurate indicator for efficient titration. Therefore, relying on objective criteria in the titration process should be advantageous. In analogy with CPAP, titration of the most optimal mandibular protrusion could be performed using RCMP during an overnight titration PSG. Recently, it was shown that titration under direct visualization of upper airway patency and collapsibility is feasible using the RCMP during DISE. However, no clinical results for such a procedure are as yet available. This study is the first to compare the most optimal mandibular protrusive position according to three titration procedures, as well as to compare the therapeutic efficacy of these titration methods.

**Trial registration:**

ClinicalTrials.gov, NCT03716648. Registered on 23 October 2018.

## Background

Obstructive sleep apnea (OSA) is a prevalent public health issue, affecting up to 17% of adult women and 34% of adult men [1]. It is characterized by repetitive episodes of partial (hypopneas) or complete (apneas) upper airway obstruction during sleep, leading to nocturnal hypoxemia and sleep fragmentation [2]. The clinical daytime consequences associated with untreated OSA include excessive daytime sleepiness (EDS), impaired cognitive performance and reduced quality of life. There is a strong correlation between OSA and both traffic and occupational accidents [3]. Furthermore, epidemiological studies provide objective evidence that OSA is an independent risk factor for cardiovascular morbidity and mortality [4–6].

The diagnostic work-up for OSA follows both subjective and objective appraisal [7]. It starts with obtaining a medical history with an emphasis on subjective symptoms, followed by a clinical assessment and an overnight sleep study for the objective diagnosis. The severity of OSA is traditionally expressed by the apnea–hypopnea index (AHI), defined as the number of apneas and hypopneas per hour of sleep [8]. Based on the AHI, the severity of OSA can be described as mild (5 ≤ AHI < 15/h), moderate (15 ≤ AHI < 30/h) and severe OSA (AHI ≥ 30/h) [8].

Due to the socioeconomic consequences and the related morbidities and mortality, adequate treatment of OSA is important. Currently, several treatment modalities are available, but in general the treatment is a stepwise approach starting with behavior modifications indicated for all patients with a modifiable risk factor. The most important conservative measure in the management of OSA is weight loss and should be advised to all overweight or obese OSA patients, as significant decrease in body weight is associated with reduced OSA severity: a reduction in weight of 10% is associated with an improvement in AHI of 26% [9]. However, it is recommended to combine weight loss and other conservative measures with nonsurgical or surgical treatment options [7].

Therapy with continuous positive airway pressure (CPAP) is the standard nonsurgical treatment option for patients with moderate to severe OSA [10]. CPAP therapy prevents upper airway collapse by providing a pneumatic splint using a constant positive pressure at the level of the collapsible segment of the upper airway throughout the respiratory cycle [11]. The amount of pressure required to avoid upper airway collapse cannot be predetermined based on OSA severity and needs to be assessed individually. To achieve the optimal pressure alleviating the disease, the current standard practice involves an overnight attended CPAP titration polysomnography (PSG) in which the applied pressure is manually increased by a sleep technician each time respiratory events occur [12]. Rather than the use of an overnight attended PSG to find the optimal CPAP pressure, an unattended auto-titrating CPAP device can be used for several nights [13, 14]. Auto-titrating CPAP devices continuously monitor the patient’s snoring, airflow and flow limitation, and provide variable CPAP pressures in accordance with respiratory events using an algorithmic approach. As such, these devices can be used either to treat a patient with different pressures delivered during different sleeping conditions, in response to differing degrees of upper airway obstruction in these states, or to identify the most appropriate fixed CPAP pressure level. More recently, Civelek et al. [12] proposed to titrate the CPAP pressure under direct visualization of upper airway collapse during drug-induced sleep endoscopy (DISE). DISE enables a dynamic, three-dimensional, real-time evaluation of the anatomical sites of upper airway collapse during drug-induced sleep which ideally mimics natural sleep, although without REM sleep being present [15]. This DISE-assisted titration showed comparable results regarding the optimal CPAP pressure that alleviates OSA as compared to the conventional titration PSG. Overall, once the optimal pressure is determined, CPAP therapy is highly efficacious in terms of alleviation of OSA severity. However, the high clinical efficacy can be compromised by low patient acceptance or suboptimal adherence, thereby limiting the overall clinical effectiveness of this therapy [16].

Another nonsurgical OSA therapy is the use of an oral appliance that is worn intraorally at night, finding retention on the teeth, and aimed at reducing upper airway collapse by protruding the mandible. Such an appliance will further be referred to as a ‘mandibular advancement device’ (MAD). Several studies in the literature compared the efficacy of MAD therapy with CPAP, showing that both treatment modalities improve the OSA severity. Although CPAP shows a greater efficacy compared to MAD therapy, comparative effectiveness and health outcomes between CPAP and MAD therapy are found. This might be explained by greater efficacy of CPAP being offset by inferior compliance relative to MAD [17].

Many designs exist, but a custom-made MAD that includes a titratable mechanism allowing for gradual protrusion is currently the preferential type [18, 19].

Based on the literature, the amount of protrusion seems to be a key factor in optimizing MAD efficacy, although more protrusion does not always yield better results [20]. Therefore, the optimal mandibular protrusion for MAD therapy needs to be determined in the individual patient and adjusted in terms of tolerability versus efficacy [21, 22]. However, up to now, no proven standard exists on how to determine this optimal MAD protrusion. So, at this stage, MAD titration remains rather ‘trial and error’ [23].

Most outcome studies on MAD therapy are using a so-called ‘subjective titration protocol’, relying on both the physical limits of the patient’s mandibular protrusion and the self-reported evolution of symptoms, such as snoring and/or daytime sleepiness [24–27]. However, such subjective improvement in symptoms may not provide the most accurate indicator for efficient titration of the MAD: it may result in a suboptimal treatment outcome, since the reduction of the subjective complaints may encourage a premature interruption of the titration [28, 29]. In an approach analogous to a CPAP titration night, the mandible could be progressively advanced during sleep, each time respiratory events occur. A so-called ‘remotely controlled mandibular positioner’ (RCMP) has been applied in overnight sleep studies to prospectively determine the optimal mandibular protrusion for MAD treatment in individual patients [21, 23, 30–32]. The literature has shown a greater reduction in AHI after RCMP titration as compared to conventional titration methods [30].

As part of the pretreatment work-up when non-CPAP treatment options are considered, DISE allows for a dynamic assessment of upper airway behavior during induced sleep, disclosing the site(s) of upper airway obstruction [33]. Recently, it was shown that the application of an RCMP during DISE is feasible and that it can be used to prospectively determine the targeted mandibular protrusion [34].

The present article proposes the protocol for a clinical study consisting of a prospective, randomized, crossover trial comparing the most optimal protrusive mandibular position as well as the treatment outcome in terms of AHI, using these three titration procedures for MAD therapy.

## Methods

### Aim, design and setting

This clinical trial proposes a prospective, randomized, crossover trial in patients diagnosed with OSA and referred for MAD treatment. Patients will be recruited from the Multidisciplinary Apnea and Snoring Clinic of the Antwerp University Hospital (Edegem, Belgium).

This study aims to compare the optimal mandibular protrusion values obtained during three titration procedures in each individual patient performed in randomized order: titration of the MAD in the home setting during 1 month based on both the physical limits of the patient’s mandibular protrusion and the resolution of subjective complaints, such as socially disturbing snoring and daytime somnolence, as currently used in routine clinical practice; an overnight titration PSG using the RCMP with stepwise mandibular protrusion until respiratory events are reduced; and titration of the mandible during DISE using the RCMP until upper airway collapse at all collapsible levels is eliminated. The DISE-assisted titration will take on average 30 min with a maximum duration of 45 min and will be carried out by an ear, nose and throat (ENT) surgeon experienced in DISE assisted by a dental sleep professional. After each type of titration, PSG-guided or DISE-assisted, respectively, in randomized order, the patient will use the MAD for 1 month in the obtained protrusion relative to the respective method. The subjective titration will also be done during a 1-month period.

A follow-up sleep study will be performed after each procedure for evaluation of the efficacy of the MAD in terms of reduction of AHI. A washout interval of 1 week between the different test conditions is integrated into the protocol. The flowchart of the protocol is shown in Figs. 1 and 2.

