#### Exclusion criteria

◦ Edentulous patients◦ Insufficient teeth to support MAD◦ Active periodontal problems including tooth mobility◦ Active temporomandibular joint dysfunction◦ Limited maximum protrusive capacity (< 6 mm)◦ Limited vertical opening (< 25 mm)◦ Enlarged palatine tonsils (Friedman grade IV tonsils)◦ Degenerative neuromuscular disorders◦ Pregnancy

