### Statistics

#### Sample size calculation

The primary endpoint of this study protocol is to assess equivalence of the protrusive position obtained with the three titration protocols. We need 65 patients to have 80% power to show equivalence of two procedures with an equivalence margin of 1.6 and a standard deviation of 3.7. These numbers are based on the results of Civelek et al. [12]. The significance level of 0.05 will be Bonferroni corrected to 0.0167, to account for comparing three titration protocols.

For every patient dropping out of the study before the first visit, an extra patient will be recruited. Based on previous studies, the dropout rate is anticipated to be around 20%, so we expect to include 78 patients in total.

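### The primary equivalence rule compares mean protrusive positions only, so it can be met while the methods give many individual patients different positions

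*Protocol article*

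**What the plan says.** The Aim, design and setting section of the protocol article states the purpose as to "compare the optimal mandibular protrusion values obtained during three titration procedures in each individual patient". The Background gives the reason: "the optimal mandibular protrusion for MAD therapy needs to be determined in the individual patient". It adds that further protrusion is not always better, and the Discussion repeats that final titration should be individual.

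Under Sample size calculation the primary endpoint is to "assess equivalence of the protrusive position obtained with the three titration protocols". The number of patients is fixed at 65, for 80% power in a comparison of two methods. The inputs to that calculation are given as "an equivalence margin of 1.6 and a standard deviation of 3.7", and the significance level of 0.05 is reduced to 0.0167 for three comparisons. Neither the margin nor the SD has a unit, and the type of SD is not stated. Both are attributed to an earlier study, which the Background and Discussion describe as a study of CPAP pressure.

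Statistical analyses specifies a linear mixed model with period, sequence and procedure as fixed effects and patient within sequence as a random effect, followed by pairwise comparisons. The article states no criterion for how closely two methods must agree within a patient.

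**The concern.** The procedure effect in this model is a difference between average positions. If DISE places one patient 5 units further forward than PSG and another 5 units further back, the pair contributes a mean difference of 0. Spread within patients enters the decision only through the width of the confidence interval, and enough patients will make that interval fit inside the margin whatever the spread.

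For a procedure whose last steps are 0.5 mm and whose purpose is to find one patient's position, this matters. The Discussion describes titration PSG as laborious and costly, and it presents the efficacy comparison as possible if the positions turn out to differ. A reader could therefore take equal means as equal positions, although most patients might have been given different ones.

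**Working it through.** **Inputs.** From Sample size calculation: margin 1.6, SD 3.7, N = 65, power 80%, alpha 0.05/3 = 0.0167. From Exclusion criteria: patients with a maximum protrusion below 6 mm are not admitted. Assumptions not in the document: true mean difference 0 and normally distributed differences.

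**Step 1: reproduce N = 65.** Take two one-sided tests on paired differences, each at 0.0167.
- Normal approximation: n = ((2.128 + 1.282) × 3.7 / 1.6)² = 62.2, so 63.
- With the t distribution (n − 1 degrees of freedom), n = 64 gives power 79.6% and n = 65 gives 80.5%. The smallest n reaching 80% is 65, as stated.

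The other readings tried do not give 65:

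| Reading | Result |
|---|---|
| Paired, one-sided 0.05 | n = 48 |
| Paired, one-sided 0.025 | n = 59 |
| Paired, one-sided 0.0083 | n = 76 |
| Two independent groups, 0.0167 | 126 per group |
| 3.7 as within-patient residual SD | power about 24% at n = 65 |

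So 3.7 acts as the SD of the difference between two methods in the same patient.

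**Step 2: individual differences implied by that SD.** P(|d| > c) = 2 × (1 − Φ(c / 3.7)).
- c = 1.6: 2 × (1 − Φ(0.432)) = 66.5%, leaving 33.5% within the margin.
- c = 3: 41.7%.
- 95% limits of agreement: ±1.96 × 3.7 = ±7.25.

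**Step 3: what the rule concludes there.** The half-width of the confidence interval is 2.175 × 3.7 / √65 = 1.00. Equivalence is therefore declared when the observed mean difference is within about 1.6 − 1.00 = 0.60 of zero. At a true mean difference of 0 this has probability 80.5% for one pair. For all three pairs together, simulation (65 patients, three equally correlated positions, SD of each difference 3.7) gives about 60% with separate paired tests and 62% with a pooled mixed-model residual.

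**Step 4: sensitivity to the SD.** Share of patients beyond 1.6, by SD of differences:

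| SD of differences | 3.7 | 2.0 | 1.5 | 1.0 |
|---|---|---|---|---|
| Beyond 1.6 | 67% | 42% | 29% | 11% |

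If 3.7 were instead the SD of a single position, the share would depend on the correlation between methods (assumed range): 76% at 0, 67% at 0.5, 54% at 0.75 and 33% at 0.9. For 80% of patients to lie within 1.6, the SD of differences would have to be about 1.6 / 1.282 = 1.25 or less.

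**The case against.** **The aim may only describe the crossover.** The sentence on each individual patient continues with the randomised order, so it can mean simply that every patient has all three procedures. The primary outcome is worded as a comparison between methods, and a mean contrast with a margin answers that. This stands as a reading of the one sentence. It does not remove the individual rationale in the Background and Discussion, which the mean contrast leaves unaddressed.

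**The protocol does not claim interchangeability.** A reader might infer that it promises DISE can replace PSG for a given patient. No section says so, and the point should not be put as if one did. What is missing is a limit on what a positive result may be taken to mean.

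**Two thirds is not a prediction.** A reader might infer that most patients will in fact differ by more than 1.6 mm. The documents do not support this: the values have no unit and come from CPAP pressure. Limits of ±7.25 read as millimetres could not describe a patient with a range of 6 mm, because the physical range would truncate the differences. This stands, and the percentages are illustrative only.

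**Disagreement is partly tested elsewhere.** Each patient wears the device at each method's position and then has a sleep study scored blind to treatment phase. AHI, snoring, sleepiness and fatigue have PSG-versus-DISE non-inferiority margins. Positional differences that cancel in a mean need not cancel in AHI. These endpoints bear on whether disagreement matters, but they are again mean or response-rate comparisons and do not measure how far positions agree.

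**An agreement table is not decisive.** Each method is applied once per patient, so limits of agreement combine disagreement between methods with each method's own repeat variability. This also stands and shapes the fix. An analysis plan that is not shown could contain such a table, but the primary endpoint, margin and model are already fixed here on means.

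**Conclusion.** The point holds in a limited form. The primary rule can support equivalence on average and nothing more, while the rationale for titration concerns the individual patient. Under the plan's own values the gap is large: about 67% of patients beyond the margin at a mean difference of 0, with about 80% probability of declaring equivalence per pair. The 80% should not be read as the chance of declaring all three methods equivalent, which is about 60%.

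These figures assume normal differences, a true mean difference of 0, and 3.7 as the SD of within-patient differences, which is inferred from N = 65 and not stated. The true share in millimetres is unknown and could be far smaller. That the rule places no limit on individual disagreement does not depend on any of these values. The mean-equivalence test is not wrong in itself; it needs a companion analysis and a bounded conclusion.

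**What to change.** 1. Keep the mean-equivalence test as the primary analysis.
2. For each pair of methods, DISE versus PSG first, prespecify Bland-Altman 95% limits of agreement and the proportion of patients whose two positions lie within the margin, each with a confidence interval.
3. State that a positive primary result means equivalent on average only.
4. State that individual agreement will be interpreted from these results together with the AHI non-inferiority results, and that with a single titration per method the observed disagreement includes each method's own repeat variability.

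**Cost.** No new data or visits are needed, since the crossover already yields paired positions. The price is one extra table and a narrower permitted conclusion. Precision at N = 65 is useful though modest: at a proportion of 33.5%, the 95% interval is about ±1.96 × √(0.335 × 0.665 / 65) = ±11 percentage points.

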**Fig. 1 Fig1:**
[figure not shown]
Schematic overview of the study design. Patients will undergo three titration procedures —subjective titration (green), titration PSG (orange) and, titration DISE (yellow) — in randomized order. This leads to six different possible sequences. A 1-week washout period is integrated between the different titration procedures. A follow-up sleep study is performed at the end of each titration method. DISE, drug-induced sleep endoscopy; MAD, mandibular advancement device; PSG, polysomnography

**Fig. 2 Fig2:**
[figure not shown]
Schedule of protocol assessments following Standard Protocol Items: Recommendations for Interventional Trials (SPIRIT). Interventions and assessments will be administered at different time points (indicated by X). See text for more details. CIS20R, Checklist Individual Strength; DISE, drug-induced sleep endoscopy; PSG, polysomnography; RCT, randomized crossover trial; VAS, visual analog scale

### Participants

Patients diagnosed with moderate to severe OSA and referred to the special care dentistry unit for treatment with an MAD will be recruited for participation in this study and will be asked for informed consent prior to the start of the study. To ensure accurately diagnosed OSA, all patients will need an initial baseline PSG of maximally 2 years old prior to the effective start of treatment, and show stable body weight (± 5 kg) since that PSG. No ENT surgery may be performed in eligible patients since the diagnostic PSG. An ENT examination, a dental screening and an appraisal of inclusion and exclusion criteria (see later) will be performed.

#### Inclusion criteria

◦ Patients with moderate to severe OSA (obstructive apnea/hypopnea index (oAHI) ≥ 15/h)◦ Age > 18 years◦ PSG < 2 years old with stable body weight (± 5 kg) and no ENT surgery since the diagnostic PSG; if body weight changes significantly or ENT surgery is performed, a new diagnostic PSG is required to confirm the diagnosis of moderate to severe OSA◦ Normal clinical and radiological (including orthopantogram X-ray), periodontal and temporomandibular joint examination◦ Subject is capable of giving informed consent◦ No documented abuses (alcohol, drugs, etc.)

#### Exclusion criteria

◦ Edentulous patients◦ Insufficient teeth to support MAD◦ Active periodontal problems including tooth mobility◦ Active temporomandibular joint dysfunction◦ Limited maximum protrusive capacity (< 6 mm)◦ Limited vertical opening (< 25 mm)◦ Enlarged palatine tonsils (Friedman grade IV tonsils)◦ Degenerative neuromuscular disorders◦ Pregnancy

